#### **8.2.2.2 Primary Analysis of Response**

The number of tumours classified as responding to treatment will be reported as a proportion of the trial set with 95%CI at 12 weeks by randomised treatment group. Response to treatment

is classified according to the WHO-RECIST criteria, where a response is either a complete response (disappearance of tumour) or a partial response (decrease in tumour volume of  $\geq 30\%$  at 12 weeks). Non-response is either stable disease (neither complete nor partial criteria met), or progressive disease (increase in tumour volume with no complete response, partial response or stable response reported before increase).

A sensitivity analysis of the Phase 2a primary outcome of response rate will be carried out on the Phase2a 'per protocol' set.

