#### **2.1.2 Cohort 2**

All tumours will contribute to the analysis based on the total number randomised (intention to treat population). A secondary analysis will be reported based on the number of tumours which have been treated for 12 weeks (per protocol population).

The primary outcome measure is the number of tumours responding to treatment by 12 weeks reported as a proportion of the number of tumours randomised in the actively and placebo groups separately.

According to WHO-RECIST criteria, a reduction in 30% volume would be sufficient to classify a 'response' to treatment in oncology. In this trial we will use this criteria as a bench mark when determining a response in this patient population. As such one of the outcomes will be to consider and confirm a definition of 'response' to treatment in this group of patients. Tumour volume will be measured on 8 - 10 predetermined identified tumours in each patient prior to randomisation (baseline) and measured again on the same tumours at 4 and 12 weeks. The change in volume for each tumour will be recorded and classified as either having a response to treatment or not.

As an early phase trial, statistical analysis will be exploratory (not based on hypothesis testing) and will be based on descriptive data presented by treatment group. Continuous measurements (including change in tumour volume from baseline) will be summarised and reported as medians and ranges (inter-quartile ranges). Categorical data (including proportions of tumours with adverse events and outcomes from the Pain Assessment Forms) will be summarised and reported as percentages and confidence intervals (95%). Since multiple tumours are sited in individual patients, a secondary analysis based on a multi-level

modelling approach will be undertaken to investigate the relationship between any change in volume and randomised treatment accounting for the multi-level nature of the tumour measurements.

QoL tools (EQ5D, DLQ) will be scored according to scoring manuals and actual scores will be reported descriptively.

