### **Cohort 2**

It is anticipated that 75 tumours could be measured in each treatment arm (150 tumours in total). Tumours receiving placebo treatment are not expected to respond to treatment, set to be very small at 5% ( $p_0$ ). This is the first exploratory trial and as such the design parameters are provided as an exemplar of the size of errors that may be anticipated with these patient numbers.

Using Fleming A'Herns early phase methodology (Fleming 1982, Ahern, 2001) any response on the experimental treatment  $<5\%$  ( $p_0$ ) would not indicate a treatment worthy of further investigation. 75 tumours recruited in the experimental arm would provide evidence of a minimum level of efficacy of approximately 15% ( $p_1$ ), indicating that a level of efficacy of  $>15\%$  would warrant further investigation, with associated error levels of 3.4% type I error ( $\alpha$ ) and 10.8% type II error ( $\beta$ ). This level of efficacy seems clinically plausible and relevant given that there is no current treatment in use for these patients.

The justification to investigate CT327 further is based on observing a minimum number of responses, referred to as the critical number (specified in the Statistical Analysis Plan). The trial will recruit an equal number of placebo-treated tumours to provide an unbiased benchmark.

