## **7. SAFETY ANALYSIS**

Most adverse events (AE) and adverse drug reactions that occur in this trial, whether they are serious or not, will be expected treatment-related toxicities due to the drugs used in this trial. For a full list of expected undesirable effects of CT327, please refer to the Investigator Brochure.

AE's are recorded by the clinical staff directly to the database on a three-point scale of severity (mild, moderate or severe) and also by causality (relationship to treatment categorised on a six point scale), as described in the protocol.

The analysis sets are the Phase 1b treatment set and the Phase 2a treatment set.

Any adverse events/reactions from start of treatment and up to the time of tumour excision (Phase 1b) or 4 weeks after end of treatment (Phase 2a), will be categorised according to severity and causality and recorded on the database.

The number of patients (Phase 1b) and tumours (Phase 2a) reporting any AE will be reported clarifying those deemed to be treatment related (Appendix 2).

In Phase 2a, the number of tumours with at least one AE will be reported as a proportion of the total number of tumours. The number of tumours with at least one treatment-related AE, that is those described as definitely, probably or possibly related, will be reported as a proportion of the total number of tumours. The number of tumours with at least one 'moderate' or 'severe' treatment-related AE will be reported as a proportion of the total number of tumours.

The unique number of patients experiencing at least one 'moderate' or 'severe' treatment-related AE will be reported as a proportion of the treatment set.

Proportions will be presented as % (95% CI).

Descriptions of the adverse events may require listing in the text.

No significance testing will be carried out.

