#### **8.2.2.1. Descriptive analysis**

Tumour volumes (mean of the three readings) will be reported descriptively as mean (standard deviation) at baseline by treatment group and overall. Tumour-level change in volume at 4 and 12 weeks will be reported as mean percentage change (with 95% Confidence interval) by randomised treatment group. Graphical representation of percentage change in tumour volume from baseline to 12 weeks will be in the form of a waterfall plot (Appendix 3).

In order to assess the possibility of differing percentage changes being influenced by initial tumour size, the mean percentage change from baseline to 4 weeks and baseline to 12 weeks will be reported by baseline tumour diameter categories. Categories will be determined by quartile measurements of baseline tumour diameter.

Mean volume and mean percentage change will be displayed graphically by treatment group and by baseline tumour diameter category.

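### The 95% intervals for tumour response and tumour-level adverse events make no allowance for four or five tumours per patient in each arm, and under-cover if tumours within a patient are positively correlated

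*Combined protocol and SAP*

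**What the plan says.** **Response.** SAP 8.2.2.2 counts responding tumours, and the count "will be reported as a proportion of the trial set with 95%CI at 12 weeks by randomised treatment group". The analysis set is the Phase 2a trial set.

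**Change in volume.** Under SAP 8.2.2.1, tumour-level change at 4 and 12 weeks "will be reported as mean percentage change (with 95% Confidence interval) by randomised treatment group".

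**Adverse events.** In SAP Section 7, for Phase 2a, "the number of tumours with at least one AE will be reported as a proportion of the total number of tumours". Treatment-related events, and moderate or severe treatment-related events, are handled in the same way. "Proportions will be presented as % (95% CI"). The section also gives one patient-level proportion, for moderate or severe treatment-related events.

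**Structure of the data.** Protocol 14.2 anticipates that "75 tumours could be measured in each treatment arm (150 tumours in total"). Protocol 7.2 expects these from 15-20 patients. SAP 3.2 has four or five tumours selected on each side of a patient, and Protocol Section 11 randomises sides, so all of a patient's tumours on one side share one treatment.

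**Where clustering is recognised.** Protocol 14.1 (Cohort 2) says "Since multiple tumours are sited in individual patients, a secondary analysis based on a multi-level" modelling approach will be carried out. SAP 8.2.2.3 specifies it as random-effects models of tumour volume, with confidence intervals, plus a repeated-measures analysis of mean volume.

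**The concern.** A binomial interval on 75 tumours treats them as 75 independent observations. Tumours in one patient share a germline mutation, one person's adherence and, within an arm, one ointment. A positive within-patient correlation is therefore plausible. If it exists, the 75 tumours carry less information than the interval claims.

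The primary outcome is affected. Because the plan rules out hypothesis testing, the per-arm interval is the planned statement of uncertainty about the response rate. SAP 8.2.2.3 calls itself a secondary analysis of the primary outcome measure, but it models volume, not response. A reader of the results would have no clustered interval for response or for tumour-level adverse events to set beside the unadjusted one.

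**Working it through.** **1. Reproduce the plan's own figure.** Protocol 14.2 gives a placebo response rate "set to be very small at 5" per cent (p0), says that 75 tumours "would provide evidence of a minimum level of efficacy of approximately 15" per cent (p1), and states errors of 3.4% and 10.8%. For X ~ Binomial(75, p) with success at X ≥ r:

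| r | P(X ≥ r), p = 0.05 | P(X < r), p = 0.15 |
|---|---|---|
| 7 | 8.1% | 5.4% |
| 8 | 3.36% | 10.82% |
| 9 | 1.2% | 18.9% |

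Only r = 8 gives both printed errors, so the design calculation treats the tumours as independent. The critical number itself is held in a separate document; 8 is inferred.

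**2. Inputs for the intervals.** n = 75 per arm; m = 4 or 5 tumours per patient per arm; true response 15%. The ICC is assumed over a range.

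**3. Approximate half-width.** Design effect DE = 1 + (m − 1) × ICC; effective n = 75/DE; half-width = 1.96 × √(0.15 × 0.85 × DE / 75). With DE = 1 this is 1.96 × √0.0017 = 8.1 points.

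| ICC | DE (m = 4, m = 5) | Effective n | Half-width, points |
|---|---|---|---|
| 0.1 | 1.3, 1.4 | 57.7, 53.6 | 9.2, 9.6 |
| 0.2 | 1.6, 1.8 | 46.9, 41.7 | 10.2, 10.8 |
| 0.3 | 1.9, 2.2 | 39.5, 34.1 | 11.1, 12.0 |

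**4. Coverage.** The half-widths above are normal approximations. Coverage was calculated separately for the exact (Clopper-Pearson) interval. Responders per patient are beta-binomial with mean 0.15 and the given ICC. The distribution of the total is the convolution over patients, and coverage is the probability of totals whose interval contains 0.15.

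| ICC | 15 patients × 5 | 19 × 4 | 20 × 4 |
|---|---|---|---|
| 0 | 96.3% | 96.3% | 97.3% |
| 0.05 | 94.3% | 94.9% | 96.1% |
| 0.1 | 92.2% | 93.3% | 94.7% |
| 0.2 | 87.9% | 90.1% | 91.9% |
| 0.3 | 83.7% | 86.8% | 88.9% |

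**5. Worked example.** Take 11 responders of 75 (14.7%). The Wilson interval has centre (p + z²/2n)/(1 + z²/n) and half-width [z/(1 + z²/n)] × √(p(1 − p)/n + z²/4n²), with z = 1.96 and n the effective sample size. Unadjusted, n = 75, it is 8.4% to 24.4%. With m = 5 it is 7.6% to 26.5% at ICC 0.1 (n = 53.6) and 6.4% to 30.1% at ICC 0.3 (n = 34.1).

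**6. Few responders.** At 5%, the placebo arm expects 0.05 × 75 = 3.75 responders. Under the 15 × 5 layout, the probability of none at all is about 4% at ICC 0.1 and 10% at ICC 0.3. With no responders a patient-level bootstrap collapses, a generalised estimating equation cannot be fitted, and no ICC can be estimated. The method chosen must work in this case.

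**The case against.** - **The intervals are not shown to be too narrow.** This stands as a condition. The SAP names no interval method, so the absence of an adjustment is read from its silence, and the documents give no ICC. At ICC 0 the unadjusted interval is valid, and at 0.05 exact coverage is 94-96%. The silence is still telling, because clustering is raised only for separate secondary models.
- **The analysis is exploratory and the decision does not use an interval.** A reader might infer that the go/no-go is distorted by these intervals. The documents do not support that: SAP 8.4 rests predominantly on the response rate and the critical number of responses, and no interval enters the rule. Clustering also affects the error rates of that count rule, but that is a separate matter and adds no weight here. Even so, a descriptive 95% interval claims 95% coverage.
- **Clustering is already handled.** This is true for volume. A reader might infer that the mean percentage change in SAP 8.2.2.1 is as exposed as response. Its interval has the same flaw, but 8.2.2.3 supplies a clustered analysis of volume with intervals. Response and tumour-level adverse events have no such counterpart.
- **Adverse events are also counted by patient.** That proportion has one observation per patient and is unaffected. It covers only moderate or severe treatment-related events.
- **Adjustment might seem to change the conclusion against the 5% benchmark.** For 11 of 75 this depends on the method. At ICC 0.3 with m = 5, a Clopper-Pearson interval on the effective n has a lower limit of 4.9%, whereas the Wilson limit is 6.4%. The example shows width and does not show a reversed finding.

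**Conclusion.** The point holds for the primary response intervals in SAP 8.2.2.2 and the tumour-level adverse event proportions in Section 7. Neither has a specified allowance for patient, and neither has a clustered analysis elsewhere. The loss is negligible at ICC 0.05 and material from about 0.2, where exact coverage at a true 15% response falls to 88-92%, and to 84-89% at 0.3. Half-widths should then be about 10 to 12 points rather than 8.1.

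These sizes rest on an assumed ICC, a beta-binomial model, equal numbers of tumours per patient, and the 15 × 5, 19 × 4 and 20 × 4 layouts. They concern per-arm intervals. An interval for the active-placebo difference would behave differently, because the comparison is within patient, and the SAP specifies none for response. The mean percentage change interval is a lesser case. Severity: should be fixed.

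**What to change.** **SAP 8.2.2.2 and the tumour-level proportions in Section 7.** Specify one method: a Wilson 95% interval on the effective sample size n/(1 + (m − 1) × ICC), where m is the number of tumours per patient in that arm. Estimate the ICC from the data and report it. Where an arm has too few responders (or tumours with events) to estimate it, for example fewer than 5, show the interval over a pre-stated ICC range such as 0.1 to 0.3. With 3.75 responders expected on placebo, this rule is likely to be needed there, so it should be written before the data are seen.

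**SAP 8.2.2.1.** Either use a patient-cluster-robust interval with a small-sample correction for 15-20 patients, or label the interval as unadjusted for patient and refer to 8.2.2.3.

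**No change** is needed to the patient-level adverse event proportion.

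**Cost.** SAP wording, a little more analysis work and wider intervals. No new data or patients are needed, and the go/no-go count rule is untouched.

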#### **8.1.2 Primary Outcome – Phase 2a**

The primary outcome measure is the proportion of tumours responding to treatment by 12 weeks. According to WHO-RECIST criteria, a reduction in 30% volume would be sufficient to classify a "response" to treatment in oncology. In Phase 2a we will use this criteria as a benchmark when determining a response in this patient population at 12 weeks.

Tumour volume will be measured on the predetermined identified tumours in each patient prior to randomisation and measured again and recorded on the same tumours at 4 and 12 weeks. We will have measures of surface area, height and volume taken 3 times at each visit for each tumour. The mean of each set of 3 measurements will be used to determine the percentage change in volume for each tumour to be able to classify tumours as having a response to treatment or not at each time point (Appendix 3).

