## 8.3 Additional Analyses

According to the WHO-RECIST criteria, a 30% reduction in volume is sufficient to classify a “response” to treatment in oncology. In this trial we use this criteria as a bench mark when determining a response in this patient population. As such a further outcome is to consider and confirm a definition of “response” to treatment in this group of patients. We will consider how many tumours are responders, stable or progressive disease at different levels of “partial response”. We will report the number of tumours who would be classified as responders for lower levels of reduction in tumour volume at both 4 weeks and 12 weeks. Response rates in the trial set will be presented in tabular form for alternative definitions, based on -5% and - 10% changes in the RECIST definition (Appendix 4).

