**Analysis of Response**

| Tumours              | Active
N= |               | Placebo
N= |               |
|-----------------------------|----------------------|---------------|-----------------------|---------------|
|                             | n (%)         | 95% CI | n (%)          | 95% CI |
| Complete Response           |                      |               |                       |               |
| Partial Response            |                      |               |                       |               |
| Total Responders     |                      |               |                       |               |
| Stable Disease              |                      |               |                       |               |
| Progressive Disease         |                      |               |                       |               |
| Total Non-responders |                      |               |                       |               |

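### Stable and progressive disease overlap in SAP 8.2.2.2, and an earlier stable or response reading bars progression, so those two rows are not reproducible

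*Combined protocol and SAP*

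**What the plan says.** SAP 8.2.2.2 counts a tumour as a responder if it disappears or if its volume falls by at least 30% at 12 weeks. For the rest it says: "Non-response is either stable disease (neither complete nor partial criteria met"; the alternative is "progressive disease (increase in tumour volume with no complete response, partial response or stable response reported before increase". Neither definition states a size of increase, and nothing ranks one label above the other.

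SAP 8.1.2 (primary outcome, Phase 2a) takes the mean of three readings per visit and uses the percentage change "to be able to classify tumours as having a response to treatment or not at each time point". Volumes are taken at baseline, week 4 and week 12.

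The split is reported in two places. The Analysis of Response table in SAP Appendix 3 has separate rows for stable and progressive disease by arm. SAP 8.3 states "We will consider how many tumours are responders, stable or progressive disease at different levels of" partial response, and the Appendix 4 table tabulates both categories at five response cut-offs from 20% to 40%. Neither place gives a progression cut-off.

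**The concern.** Three features of the wording cause trouble.

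- **Overlap.** A tumour that has doubled in size meets neither response criterion, so it meets the stable definition. It may also meet the progressive one.
- **No minimum increase.** Where no earlier label blocks it, a rise of any size counts, including one that is only measurement error. At week 4 no post-baseline reading comes first, so every rise there meets both definitions.
- **Look-back clause.** A stable or response reading before the increase rules out progression. Week 4 is the only earlier post-baseline visit, so it decides whether growth at week 12 can be called progressive.

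At stake is the only categorical count of tumour growth by arm. Two analysts following the SAP faithfully could fill the same row with very different numbers, and a choice made after unblinding could favour one arm.

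**Working it through.** **Inputs.** Response cut-off of 30% and category definitions: SAP 8.2.2.2. Visits and mean of three readings: SAP 8.1.2. 75 tumours per arm, p0 = 5%, p1 = 15%, type I error 3.4%, type II error 10.8%: protocol 14.2. Measurement error is not given, so it is assumed equal and independent at each visit. Increase is taken as increase from baseline.

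**Step 1: the plan's own figure.** With success defined as at least r responders in 75, exact binomial probabilities at r = 8 are P(X ≥ 8 | 5%) = 0.0336 and P(X ≤ 7 | 15%) = 0.1082. These match 3.4% and 10.8%. Neighbouring values do not: r = 7 gives 8.1% and 5.4%, and r = 9 gives 1.2% and 18.9%. The critical number is held in a separate file, so 8 is inferred. The calculation uses responders against non-responders only, so moving tumours between two non-response rows leaves it unchanged.

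**Step 2: three ways to apply the wording at week 12.**

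- A: stable is taken literally at week 4. Every tumour then has an earlier complete, partial or stable label, and none can ever be progressive.
- B: a rise at week 4 is called progressive, and only a fall short of 30% or no change is called stable.
- C: the look-back clause is not applied, for example because only the week-12 label is treated as reported. This departs from the words.

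| Week 4 | Week 12 | A | B | C |
|---|---|---|---|---|
| -2% | +80% | stable | stable | progressive |
| -35% | +10% | stable | stable | progressive |
| -5% | +1% | stable | stable | progressive |
| +1% | +1% | stable | progressive | progressive |
| +1% | +40% | stable | progressive | progressive |

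All five tumours meet the stable wording at week 12. The responder count is the same under A, B and C.

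**Step 3: tumours with no true change.** Let V0, V4 and V12 be the three visit means. They are exchangeable.

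- A: 0, so 0 of 75.
- B: P(V4 > V0 and V12 > V0) = P(V0 is the smallest of three) = 1/3, so 75/3 = 25 tumours.
- C: P(V12 > V0) = 1/2, so 75/2 = 37.5 tumours.

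These shares do not depend on the size of the error. Simulation gave 33% and 50% for B and C at every coefficient of variation (CV) tried.

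**Step 4: tumours that truly grow (assumed figures).** With +10% at week 4, +30% at week 12 and a CV of 10% for the visit mean, the share labelled progressive is 0% (A), 74% (B) and 97% (C).

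In a second scenario, +8% at week 4 and +25% at week 12, take the tumours above baseline at week 12. Under B, the share labelled stable because the week-4 reading was at or below baseline is:

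| CV of visit mean | 3% | 5% | 10% | 15% |
|---|---|---|---|---|
| Labelled stable | 3.5% | 14% | 27% | about 31% |

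**The case against.** The strongest reply is that little depends on these labels. Both count as non-response, and the primary result is binary: "The number of tumours classified as responding to treatment will be reported as a proportion of the trial set with 95%CI" by randomised group. The trial is descriptive. Growth by arm is also reported without the labels:

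- SAP 8.2.2.1 gives mean percentage change with confidence intervals at weeks 4 and 12, and a waterfall plot.
- SAP 8.2.2.3 gives multilevel and repeated-measures models.
- SAP Appendix 3 tabulates volume by visit and change by baseline diameter.

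All of this stands. It defeats a stronger reading that a reader might reach, namely that the trial would hide late growth. A tumour at -2% and then +80% is stable in one row but appears as +80% on the waterfall plot. Protocol 17.3 does exclude growth from serious adverse events, but its stated reason is that tumour size is already documented and monitored as the primary outcome. That points to measured volume, not to these labels.

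Two other inferences also fail. It is tempting to say that a third to a half of unchanged tumours will be called progressive, but the literal reading gives none. It is also tempting to quote about 30% of growing tumours called stable, but that is the top of an assumed range starting at 3.5%. The documents give no measurement error, and protocol 13.2 calls the imaging system highly sensitive and reproducible.

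The reply does not repair the wording. Averaging three readings reduces noise but sets no threshold and no precedence. The other analyses do not make the two rows reproducible.

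**Conclusion.** The point holds as a defect of reporting and reproducibility. As written, the two categories overlap, progression has no minimum size, and a stable or response reading at week 4 blocks progression at week 12. Among unchanged tumours the progressive row could read 0%, about 33% or about 50%, or 0, 25 or about 37 of 75. This assumes only equal independent error at each visit. How much real growth would be labelled stable depends on a measurement error that the documents do not state, so it can be given only as a range.

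The effect is confined to the stable and progressive entries of SAP Appendices 3 and 4. The responder proportion, its confidence interval, the critical-number decision and the continuous volume analyses do not change. This is more than missing detail, because a stated rule gives wrong rows for tumours that grow late. It is not a bias in the primary endpoint.

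**What to change.** Amend SAP 8.2.2.2, and carry the change into SAP 8.3 and Appendices 3 and 4:

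1. Classify each tumour at each visit against baseline only, as exactly one of complete response, partial response, stable or progressive.
2. Delete the clause that makes progression depend on earlier readings.
3. Define stable as neither complete response, partial response nor progressive.
4. Fix one minimum increase for progression before unblinding. Justify it by the measurement error estimated from the three replicate readings per visit, and hold it constant across the Appendix 4 rows.

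The minimum increase should not simply mirror the 30% response cut-off. The documents give no basis for that value. In the +8%/+25% scenario it would place 82%, 71%, 58% and 50% of tumours above baseline at week 12 in the stable row at CVs of 3%, 5%, 10% and 15%, which is more than the current wording does under reading B.

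The cost is one paragraph of SAP text and matching table notes. No new data are needed and the primary responder count is unchanged. The downside is that any growth threshold is partly a convention, so the waterfall plot and mean percentage change should remain the main description of growth.
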